#### **Timeline:**

2014 fall: Planning, design, inclusion of collaborators.

2015: Application to REK, register in Clinical Trials, Apply for funding, Hire Project coordinator, project assistants and audiographers.

2017 fall: Begin data collection. Estimated time 2.5 years.

2019 fall: Begin 2-year controls after operation, estimated time 2.5 years.

2020 fall: Begin qualitative study, own institution.

2021 spring: Begin qualitative study in different parts of Norway.

2022 spring: Hire PhD stipendiat when 2-year data is finished being collected.

2022-2025: Analysis and article writing.

2021 fall: Begin 4-year control after operation, estimated time 2.5 years (finished spring 2024)

2024: Hire new post-doc/stipendiat as needed.

2027: Planned end to study.

|------------------|-------------|---------------------------|--------------------------------------|----------------------------------|
| 1.0              | 1.0         | NA                        | First edition of SAP                 | October 31 st
2023 |

### 3. Abbreviations

|       |                                |
|-------|--------------------------------|
| PTA   | Pure tone average              |
| VT    | Ventilation tube               |
| GP    | General practitioner           |
| HRQoL | Health-related quality of life |
| SD    | Standard deviation             |
| ENT   | Ear, Nose and Throat           |
| LMM   | Linear Mixed Models            |

## 4. Introduction

### 4.1 Background and rationale

Otitis media with effusion is a major cause of acquired hearing problems in children. Operative treatment with the implantation of ventilation tubes (VTs), also called tympanostomy tubes or grommets, is indicated in cases of persisting or recurrent otitis media. This is the most common ambulatory surgery performed on children, and in Norway approximately 6700 children undergo surgery annually. Post-operative controls are predominantly carried out by otolaryngologists within the specialist health care system and may continue for two or more years. These controls are performed to assess whether the tubes are functional, whether hearing loss has improved and to properly treat potential complications. A meta-analysis performed in 2001 concluded that sequelae after VTs are most often transient or cosmetic in nature. VT removal is recommended after 2 years if they have not been spontaneously expelled. This is done to reduce the risk for a persistent perforation of the tympanic membrane.

The ConVenTu study is a multicenter randomized non-inferiority study which compares the hearing of patients treated with tympanostomy tubes where controls were performed by a general practitioner (GP), to those controlled within the specialist health care system. The aim is to determine whether controls performed by the GP are a safe and sufficient alternative to those controlled within the specialist health care system.

### 4.2 Trial objectives

The primary objective of this study is to determine whether there is a difference in middle ear function in patients where post-operative controls were performed by the GP compared to those controlled within the specialist health care system.

## 5. Trial methods

### 5.1 Trial design

This is a multicenter randomized non-inferiority study involving six centers in Norway and organized through St. Olavs Hospital, Trondheim, Norway. Patients were included through Gjøvik hospital, Stavanger University Hospital, hospitals in Ålesund and Molde as well as a private practice in Kristiansund. An initial assessment of eligibility was performed through the out-patient ENT clinic upon further referral for operative implantation of tympanostomy tube(s). The surgical procedure was performed at one of the aforementioned hospitals.

### 5.2 Randomization

The randomization procedure is computerized and carried out utilizing the “WebCRF” software developed at the Unit for Applied Clinical Research at The Faculty of Medicine and Health Sciences, NTNU. The design is block randomization with blocks of varying sizes, with an allocation ratio of 1:1, stratified on the study center.

### 5.3 Sample size

The sample size was calculated prior to inclusion by a statistician. Hearing thresholds are determined in 5 dB steps and equality in PTA 2 years after surgery (primary endpoint) was

therefore defined as  $< 5$  dB (5 dB as equivalence margin). To avoid an incorrect conclusion of ‘no difference’ between the groups (type II error), the power of the tests for detecting a difference of  $\geq 5$  dB must be high ( $\geq 95\%$ , error margin  $< 5\%$ ). Thus, with a power of 95% and a significance level of 5% (two-sided test), 105 participants are needed in each group to be able to detect an absolute difference in mean PTA between the groups of  $\geq 5$  dB (SD 10 dB) in each group based on the results of our previous study. 15% was added to mitigate a potential skew distribution of hearing level, and an additional 20% to account for potential dropouts, we are left with a sample size of 145 participants in each group. To maintain power in an analysis stratified for six study centers (five additional parameters in model), the total sample size must be increased by at least 50 participants, applying the general rule of thumb of at least 10 cases per parameter. If we assume that the 50 participants are evenly distributed in the two randomization groups, this leaves us with a sample size of at least 170 participants in each group. We initially planned to truncate up to 200 participants in each group to maintain power in case of a higher dropout rate. However, during the pandemic the surgery rate in Norway dropped dramatically, and with it our inclusion rate. After a preliminary assessment of our drop-out rate and recalculation by the project’s statistician, it was determined that 135 participants in each group would be sufficient.

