### **Number of participants**

The calculation of the number of participants was performed by the statistician. The number depends on which factors which are to be analyzed and which statistical method will be used. We are interested in determining differences in effect of treatment in disfavor of the GP-group, but a better result in this group would be optimal in regards to the clinical implications (performing therefore a two sided test. No difference between groups is also a possibility and of interest (equivalence study). With a focus on the likeness between groups it is especially important to avoid falsely concluding “no effect” (type II error), which implies that we want a high power for the test for difference between groups, minimum 90%, preferably up to 95%.

The primary end-point is hearing, which is measured in dB (continuous variable). We examine changes in average hearing in the frequencies 0,25-4,0 kHz between 2 timepoints. The smallest clinically relevant change in hearing is 5dB. With an expected bettering of 10dB in the one group and 5dB in the other group (absolute diff. 5dB), and estimated standard deviation of 10dB in each group, we would with a significance of 5% need 85 (105) participants in each group to determine a difference with 90% (95%) power. To account for skew from the normal distribution, at least 15% should be added (increase to 98 or 131 in each group) and an additional 20% for drop-outs. A minimum of at least 118(157) participants in each group would be required. To maintain power in a model where we account for study center (random factor), and other clinical or demographic factors, the number must be increased (by at least 10 cases per variable. The total is now increased from 314 to 400, 200 participants in each group due to multiple participating hospitals.

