# 8. Analysis

## 8.1 Analysis of the primary efficacy endpoint

### 8.1.1 Pure tone average (PTA)

The primary outcome will be the mean change in PTA from baseline between those patients controlled by their general practitioner and those controlled through the specialist health care system. PTA will be measured by taking the mean of the hearing thresholds in dB measured at 500Hz, 1kHz, 2kHz and 4kHz using pure tone audiometry.

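### SAP 5.3 sizes the trial on PTA at 2 years, SAP 5.4.1 and 8.1.1 analyse change in PTA, and neither document says which of the two the 10 dB SD describes

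*Combined protocol and SAP*

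**What the plan says.** The sections that define the endpoint and the sample size do not agree.

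- **SAP 5.3 (Sample size)** works on the level of hearing at 2 years: "equality in PTA 2 years after surgery (primary endpoint) was" set at less than 5 dB. It continues: "105 participants are needed in each group to be able to detect an absolute difference in mean PTA between the groups" of at least 5 dB. The SD is given as "SD 10 dB) in each group based on the results of our previous study".
- **SAP 5.4.1 (Hypothesis test)** measures change between baseline and the 2-year visit. Its alternative hypothesis sets mean change in the GP arm against PTA in the specialist arm, so both variables appear in one sentence. Superiority of specialist follow-up is to be claimed from the test of change from baseline.
- **SAP 8.1.1** reads: "The primary outcome will be the mean change in PTA from baseline between those patients controlled by their general practitioner" and those followed by specialists.
- **SAP 8.1.2** plans two analyses. One is a linear mixed model with a single common baseline level, comparing mean PTA at 2 years. The other is a t-test on mean change. Neither is named as primary.
- **Protocol, Number of participants**, works on change between two time points: "With an expected bettering of 10dB in the one group and 5dB in the other group (absolute diff. 5dB), and estimated standard deviation of 10dB". From this it obtains 85 per group for 90% power and 105 for 95%.

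No section gives a baseline SD or a correlation between visits, or says whether the earlier study supplied an SD of 2-year PTA or of change.

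**The concern.** PTA at 2 years and change in PTA are different variables and in general have different SDs. Randomisation makes the expected difference between arms the same for both, so the 5 dB carries over. The SD does not carry over without further information. The same 5 dB, 10 dB and 105 per group are nevertheless attached to change in the protocol and to level in SAP 5.3.

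This matters because SAP 5.3 asks for power of at least 95% specifically to guard against a wrong conclusion of no difference. A reader cannot tell whether that assurance belongs to the outcome in 8.1.1, to the mixed model in 8.1.2, or to both. With two unranked analyses on two variables, the decision rule is also open if they disagree.

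**Working it through.** **Inputs.** From SAP 5.3: difference 5 dB, SD 10 dB, two-sided 5%, power 95%, 105 per group, 20% drop-out, final target 135 per group. From SAP 5.2: 1:1 allocation. Assumed, because not given: the baseline-to-2-year correlation r and the baseline SD.

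**1. The plan's own figure.** n per group = 2 × SD² × (1.960 + 1.645)² / 5² = 2 × 100 × 12.996 / 25 = 103.97, so 104; the exact t calculation gives 105. The protocol's 90% figure also reproduces (85 by normal approximation, 86 by t). Power at 105 = Φ(5 / (10 × √(2/105)) − 1.96) = Φ(3.623 − 1.96) = 95.2%.

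**2. Reading A: 10 dB is the SD of PTA at each visit.** The SD of change is √(s0² + s1² − 2·r·s0·s1), where s0 is the baseline SD and s1 the 2-year SD. With both at 10 dB this is 10 × √(2(1 − r)). The last column uses 135 × 0.8 = 108 completers.

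| r (assumed) | SD of change, dB | Power of change t-test, 105 per group | n per group for 95% | Power, 108 per group |
|---|---|---|---|---|
| 0.2 | 12.65 | 81.7% | 167 | 82.8% |
| 0.3 | 11.83 | 86.5% | 146 | 87.4% |
| 0.4 | 10.95 | 91.1% | 125 | 91.8% |
| 0.5 | 10.00 | 95.2% | 104 | 95.7% |
| 0.6 | 8.94 | 98.2% | 84 | 98.4% |

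These figures include no allowance for skew or centre.

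**3. Reading B: 10 dB is the SD of change.** The t-test on change has 95.2% power at every r. An unadjusted comparison of 2-year PTA would then have SD 10 / √(2(1 − r)) with equal visit SDs: power 97.8% at r = 0.4, 95.2% at 0.5, 90.0% at 0.6 and 80.1% at 0.7.

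**4. Unequal visit SDs.** If the 2-year SD and the SD of change are both 10 dB, then 100 = s0² + 100 − 20·r·s0, so r = s0/20: 0.4 for a baseline SD of 8 dB, 0.5 for 10 dB, 0.6 for 12 dB. With a 2-year SD of 10 dB and r = 0.5, a baseline SD of 8, 12 or 14 dB gives SD of change 9.17, 11.14 or 12.49 dB, and power 97.7%, 90.2% or 82.7%.

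**5. Baseline-adjusted 2-year PTA.** Its residual SD is s1 × √(1 − r²), which cannot exceed s1. Since the variance of change equals s1²(1 − r²) + (s0 − r·s1)², it cannot exceed the SD of change either. It is therefore at most 10 dB under either reading, whatever the baseline SD. At r = 0.3 with equal visit SDs it is 9.54 dB (power 96.7%) under A and 8.06 dB (99.4%) under B. For r from 0 to 0.8, power at 105 per group is never below 95.2%. The mixed model in 8.1.2 has one common baseline mean and so also uses the baseline; its power is approximately this.

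**The case against.** The strongest reply is that there was one calculation, made on change and loosely reworded in the SAP. The protocol ties 10 dB to improvement, and SAP 5.3 says the calculation preceded inclusion and repeats the same 5 dB, 10 dB, 95% and 105. On that reading the 8.1.1 outcome has its stated power and the table under reading A does not apply. This is plausible and cannot be excluded, but SAP 5.3 would then still misname the endpoint.

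A second reply is that the mixed model comes first in 8.1.2, the t-test is added after it, and the model approximately keeps 95% under either reading. That stands on precision. It does not settle the decision rule, because 8.1.1 names change as the outcome and 5.4.1 rests the superiority claim on the test of change.

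A reader might infer that the stated power holds only if the visits correlate at exactly 0.5. The documents do not support this. The value 0.5 is where the SDs of level and change coincide when visit SDs are equal. Under reading A any r of 0.5 or more gives at least 95% for change; under reading B the change outcome has 95% whatever r is.

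A reader might also infer that r is low, since the protocol expects fluid in 80–90% of children before operation and amelioration in 85–90%. That makes a low r conceivable but supplies no value, and it equally casts doubt on equal visit SDs.

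**Conclusion.** The endpoint and its SD are inconsistent between SAP 5.3 and SAP 5.4.1 and 8.1.1, and between SAP 5.3 and the protocol. It is not an arithmetic error: 105 per group is correct for a 5 dB difference with SD 10 dB.

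A loss of power arises for the t-test on change if 10 dB is the SD of PTA at each visit and r is below 0.5 (equal visit SDs assumed). With 105 per group, power is then about 91% at r = 0.4 and 87% at r = 0.3. Unequal visit SDs move these figures in either direction. If 10 dB is the SD of change, the change outcome loses nothing.

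It would be tempting to conclude that the trial is underpowered. The documents do not support that: they give neither r nor a baseline SD, and the planned mixed model approximately keeps the stated power. What they do support is that the 95% claim is not tied to one defined endpoint and one primary analysis.

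**What to change.** 1. In SAP 5.3, 5.4.1, 8.1.1 and 8.1.2, name one primary endpoint and one primary analysis: PTA at 2 years compared between arms with adjustment for baseline PTA, by the common-baseline mixed model or by ANCOVA. Base the decision rule in 5.4.1 on that analysis and make the t-test on change supportive.
2. In 5.3, state whether the 10 dB from the previous study is the SD of 2-year PTA or of change. This has to be looked up in the sponsor's data; neither answer should be presumed.
3. If change analysed by t-test is to stay primary, give its SD from the previous study in 5.3 and restate the power at 105 per group and at the completers expected from 135 per group (108 with the planned 20% loss).

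The cost is SAP wording and one look-up in the sponsor's earlier data, best done before the group codes are revealed. Under option 3 the restated power could be less favourable. No extra patients are needed, and the recommended primary analysis is close to the model already planned.

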## 5.4 Statistical framework

### 5.4.1 Hypothesis test

Primary outcomes will be determined by measuring the change in the average of measured frequencies between 500Hz and 4kHz between baseline and control 2 years after the operative implantation of tympanostomy tubes. The null hypothesis is that controls performed by the GP lead to poorer PTA results 2 years after implantation of tympanostomy tubes compared to those performed within the specialist health care system. The alternative hypothesis will be that the mean change in PTA of patients controlled by their GP is not inferior to the PTA of patients controlled in the specialist health care system.

The test will be performed at the two-sided 5% significance level. A difference between the two groups will be claimed if the null hypothesis is rejected (p-value less than 5%). Superiority of controls within the specialist health care system will be claimed if the two-sided p-value in the test comparing the change from baseline is less than 5% and if the effect goes in favor of controls performed within the specialist health care system.

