### **Statistical analysis**

Linear mixed model (LMM) with center as random factor will be used to examine if there is a significant long-term effect (at 2 and 4 years) of treatment (insertion of drain) on hearing level and other audiological and clinical factors. Interaction joints will be included in the statistical model to examine the effect of treatment, measured in the form of change compared to pre-operative measurements, is the difference between patients who receive

follow-up through their GP or hospital. Log transformation of data will be actual if it is relevant to study relative over absolute changes, and transformation of data will be actual if a response variable appears to be skewed. Alternative non-parametric models can be used as needed.

Differences between the two randomization groups (hospital, GP) taking into account severity of complications, number of reoperations and proportion of re-referrals under the follow up period will be examined with the help of chi-squared tests (as a categorical variable) or Mann-Whitney test of differences of the entirety. It will also be actual to compare groups taking into account re-operation rate, and identify riskfactors for recurrence (re-operation), by using different types of survival analysis models, alternatively a logistic regression (if one can not account for time for re-operation).

If there is no significant difference between groups, we will focus on magnitude of differences between groups. With a lack of significant difference we will use a 95% confidence interval for absolute difference around 0 (around 1 for relative difference), but border values in the interval must be less than that which is considered a clinical difference of significance. What these values are will depend on which factors are being analyzed.

The health economic analyses will be performed based on randomization and where follow up has been performed.

In the qualitative portion of the study the transcription of interviews will be done continuously. Multiple researchers belonging to the research group and the project will collaborate to read and analyze the transcript. The analysis method will be adjusted to the data and presented problems.

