## 6. Statistical principles

### 6.1 Confidence intervals and p-values

All calculated p-values will be 2 sided and compared to a 5% significance level. If a p-value is less than 0.05, the null hypothesis will be discarded. Efficacy estimates for the two alternatives will be presented with two-sided 95% confidence intervals.

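### SAP 5.4.1 and 6.1 give no rule for concluding non-inferiority: the hypotheses and test omit the 5 dB margin, and the claim sentences contradict the null hypothesis

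*Combined protocol and SAP*

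**What the plan says.** **Design.** SAP 5.1: "This is a multicenter randomized non-inferiority study involving six centers in Norway". SAP 4.1 says the same. The objective in SAP 4.2, however, is worded as a difference: "to determine whether there is a difference in middle ear function".

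**Hypotheses (SAP 5.4.1).** "The null hypothesis is that controls performed by the GP lead to poorer PTA results 2 years after implantation of tympanostomy tubes", compared with specialist follow-up. Under the alternative, the mean change in PTA with GP follow-up "is not inferior to the PTA of patients controlled in the specialist health care system". Neither statement contains a figure.

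**Claim rules (SAP 5.4.1).** The test is two-sided at 5%. "A difference between the two groups will be claimed if the null hypothesis is rejected (p-value less than 5" per cent). The next sentence claims superiority of specialist follow-up if p is below 5% and the effect favours it. There is no third rule.

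**SAP 6.1.** "If a p-value is less than 0.05, the null hypothesis will be discarded". Two-sided 95% intervals are to be presented, but they are not compared with anything.

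**SAP 8.1.2.** A linear mixed model and a t-test of mean change are planned, neither with a margin.

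**Where the margin stands.** SAP 5.3 names "5 dB as equivalence margin" when deriving the sample size. The protocol, under Number of participants, also gives 5 dB as the smallest clinically relevant change in hearing.

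**Protocol, Statistical analysis.** "With a lack of significant difference we will use a 95% confidence interval for absolute difference around 0". The same sentence then requires the limits of that interval to be smaller than a clinically important difference. The values are said to depend on the variable analysed.

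**The concern.** A non-inferiority conclusion needs three things: a margin in the null hypothesis, a test or interval set against that margin, and a sentence saying which result supports the claim. SAP 5.4.1 and 6.1 have none of them. What they describe is a two-sided test of zero difference attached to a null hypothesis that is not zero difference.

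The sentences also conflict. Take p<0.05 with the effect favouring specialist care. Under 6.1 the null that GP is poorer is discarded, which formally leaves the alternative that GP is not inferior. Under 5.4.1 the same result is a claim of specialist superiority.

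At stake is the conclusion the trial was set up to reach. Without a prespecified rule, its reading would be settled after the results are known. A non-significant result could be reported as no difference although the interval passes 5 dB. A small significant difference lying inside the margin could be reported as specialist superiority with no statement on non-inferiority.

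**Working it through.** **Inputs.** From the documents: margin 5 dB, SD 10 dB, two-sided 5%, 95% power, 105 per group before inflation, final target 135 per group (SAP 5.3). Assumptions: SD 10 applies to the change in PTA; 108 evaluable per arm, that is 135 × 0.8, borrowing the plan's 20% drop-out allowance because the observed rate behind the 135 is not reported; SDs of 12 and 14 dB as an illustrative range only. Let d be the estimated amount by which GP is worse than specialist care.

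**1. The plan's own figure.** n = 2 × (1.96 + 1.645)² × 10²/5² = 103.97, so 104 by the normal approximation; the exact t calculation gives the stated 105. Then 105 × 1.15 × 1.20 = 144.9, the stated 145. The final 135 cannot be reproduced from what is given.

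**2. Where the two rules part.** SE = SD × √(2/n). The difference test is significant when |d| > 1.96 × SE. A margin rule concludes non-inferiority when d + 1.96 × SE < 5, that is d < 5 − 1.96 × SE.

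| Evaluable per arm | SD (dB) | SE | Significant against GP if d exceeds | Non-inferior if d is below |
|---|---|---|---|---|
| 108 | 10 | 1.361 | 2.67 | 2.33 |
| 108 | 12 | 1.633 | 3.20 | 1.80 |
| 108 | 14 | 1.905 | 3.73 | 1.27 |
| 135 | 10 | 1.217 | 2.39 | 2.61 |

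With 108 and SD 10, estimates of 2.33 to 2.67 dB are non-significant but fail the margin; the upper limit can reach 2 × 2.67 = 5.33 dB. With 135 and SD 10 that zone does not exist. Instead, estimates of 2.39 to 2.61 dB are significant against GP and also within the margin.

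**3. How often an estimate falls in the zone at SD 10.** If the groups are truly equal: for 108, Φ(2.667/1.361) − Φ(2.333/1.361) = 0.975 − 0.957 = 1.8%; for 135, Φ(2.614/1.217) − Φ(2.386/1.217) = 0.984 − 0.975 = 0.9%.

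**4. If non-significance alone were read as no difference.** With a true 5 dB deficit and 108 per arm, the chance of a non-significant result is Φ(1.96 − 5/SE): 4.3% at SD 10, 13.5% at SD 12, 25% at SD 14. Under a margin rule it is Φ((5 − 1.96 × SE − 5)/SE) = Φ(−1.96) = 2.5% at any SD.

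**5. The null taken as written, without a margin.** Rejecting that GP is poorer would require GP to be shown better. If the groups are truly equal, that happens 2.5% of the time. The 5 dB margin test would conclude non-inferiority with probability Φ(5/SE − 1.96) = 95.7% (108) or 98.4% (135).

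**6. Sample size after the change.** Non-inferiority at one-sided 2.5% uses the formula in step 1 with the same inputs, so 104 (105 exact) is unchanged. Two-sided equivalence at the same level and 95% power needs 2 × (1.96 + 1.96)² × 10²/5² = 122.9, so 123 per group.

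**The case against.** The strongest reply is that the documents, read together, already hold an interval rule. The protocol says that after a non-significant test the 95% limits must be smaller than a clinically important difference, and both documents put that at 5 dB for hearing. Under that rule, a true 5 dB deficit with 108 per arm would be wrongly passed about 2.5% of the time, not 4.3% to 25%. This stands. The larger rates apply only to a reader who stops at the p-value, and the two largest also depend on SDs that the documents do not give. What remains is that the protocol rule starts only after non-significance, so it is silent on the 2.39 to 2.61 dB zone, and that the SAP does not repeat it.

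A reader might also infer that the SAP inverts the conclusion, so that a harmful result would be declared non-inferior. The documents do not support that: 5.4.1 gives such a result an explicit claim in the correct direction, specialist superiority. The text contradicts itself; it does not instruct anyone to declare GP follow-up non-inferior.

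Nor is the margin missing from the plan. It is in SAP 5.3, and because 6.1 requires 95% intervals, a reader could compare them with 5 dB. The gap is that no SAP sentence makes that comparison the decision.

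**Conclusion.** The point holds as a fault in the decision rule. SAP 5.4.1 and 6.1 omit the margin, contradict themselves on what rejection means, and never say when non-inferiority is concluded; the protocol's partial rule does not fill the gap. It should be corrected because it governs the primary conclusion.

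The numerical size is modest at the planned SD of 10 dB: the conflicting zones are 0.34 dB wide (108 evaluable, assumed) and 0.23 dB wide (135), with at most a 1.8% chance of an estimate landing there if the groups are truly equal. The zone with 108 per arm widens if the SD is larger, to 1.80–3.20 dB at an assumed 12 and 1.27–3.73 dB at an assumed 14. All figures use the normal approximation and take SD 10 as the SD of the change.

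**What to change.** In SAP 5.4.1 and 6.1:

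- State H0: GP follow-up is worse than specialist follow-up by at least 5 dB in mean change in PTA from baseline to 2 years, the primary outcome in 5.4.1 and 8.1.1. State H1: worse by less than 5 dB.
- Conclude non-inferiority if the limit of the two-sided 95% confidence interval in the direction of harm to GP is below 5 dB, whatever the p-value for zero difference. Say which of the two analyses in 8.1.2 supplies that interval.
- Make superiority in either direction a separate second step, reported beside the margin.
- Delete the sentence that turns rejection of the null into a claim of a difference.
- Confirm that non-inferiority is meant, as in 4.1 and 5.1, and replace the equivalence wording in 5.3.

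The cost is SAP wording, with no new data or participants, and the base 105 per group stands. That depends on the last item: if two-sided equivalence is intended, about 123 per group would be needed for 95% power at the same level, and 5.3 would have to be reworked.
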